## Abstract

Introduction: Patients with neurogenic lower urinary tract dysfunction (NLUTD) reliant on intermittent self-catheterization for bladder emptying are at an increased risk of recurrent urinary tract infections (rUTI). So far, the most common practice in the prevention of rUTIs is long-term low-dose antibiotic prophylaxis, phytotherapy, and immunomodulation, whereby antibiotic prophylaxis inevitably leads to the emergence of drug-resistant pathogens and difficulty in treating infections. Therefore, non-antibiotic alternatives in the prevention of rUTIs are urgently required. We aim to identify the comparative clinical effectiveness of a non-antibiotic prophylaxis regimen in the prevention of recurrent urinary tract infections in patients with neurogenic bladder dysfunction who practice intermittent self-catheterization. Methods and analysis: In this multi-centre, prospective longitudinal multi-arm observational study, a total of 785 patients practising intermittent self-catheterisation due to NLUTD will be included. After inclusion, non-antibiotic prophylaxis regimens will be instilled with either UroVaxom^®^ (OM-89) standard regimen, StroVac^®^ (bacterial lysate vaccine) standard regimen, Angocin^®^, D-mannose (oral dose 2 g), bladder irrigation with saline (once per day). The management protocols will be pre-defined, but the selection of the protocol will be at the clinicians’ discretion. Patients will be followed for 12 months from the onset of the prophylaxis protocol. The primary outcome is to identify the incidence of breakthrough infections. The secondary outcomes are adverse events associated with the prophylaxis regimens and the severity of breakthrough infections. Other outcomes include the exploration of change in susceptibility pattern via the optional rectal and perineal swab, as well as health-related quality of life over time (HRQoL), which will be measured in a random subgroup of 30 patients. Ethics and dissemination: Ethical approval for this study has been granted by the ethical review board of the University Medical Centre Rostock (A 2021-0238 from 28 October 2021). The results will be published in a peer-reviewed journal and presented at relevant meetings. Study registration number: German Clinical Trials Register: Number DRKS00029142.

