We have recourse to a broad armamentarium of non-antibiotic options, whereby significant evidence is limited. Several viable and readily available options have been shown to yield consistent results. Main alternatives to antibiotic prophylaxis include vaccines, antiseptics, urine-specific antimicrobials, and direct mechanic washouts of the bladder. A variety of vaccines have been used in the prevention of rUTIs. Especially OM-89 (Urovaxom^®^) and the bacterial lysate vaccine Strovac^®^ have been diligently tested and proven to lower the rate of UTI [3,4,5,6]. Additionally, a wide variety of phytotherapeutics is currently in use, especially in Eastern medicine, as a cost-effective and low-threshold, whereas ambivalent efficacy has been reported. A combination of Tropaeoli majoris herba (Nasturtium) and Armoraciae rusticanae radix (Horseradish) demonstrated excellent safety and efficacy in the prevention of recurrent UTIs [7,8]. D-Mannose is another beneficial and cheap prophylactic, therapeutic agent in rUTI with very few side effects [9,10]. Bladder irrigation with various agents, e.g., neomycin, acetic acid, or sterile saline, is also widely used in order to lower bacterial load and defer sedimentation [11,12,13]. 

The main aim of our study is to identify the comparative clinical effectiveness of non-antibiotic prophylaxis regimens in the prevention of rUTI infections in patients with neurogenic bladder dysfunction who practise clean intermittent self-catheterization (CISC). The primary outcome is depicted by the number of breakthrough infections. Secondarily adverse events associated with the prophylaxis regimens and the severity of breakthrough infections must be investigated. 

Change in susceptibility pattern via the optional rectal and perineal swab, as well as health-related quality of life over time (HRQoL) outcomes, will be measured in a random subgroup of 60 patients.

The primary objective is to identify the clinical effectiveness of different prophylactic regimens. The secondary objective is to determine the adverse events related to prophylaxis and the severity of breakthrough infections. 

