## 3. Design

This is a prospective, longitudinal, multi-arm, multi-centre, observational, clinical cohort study. Patients will receive approved non-antibiotic UTI prophylaxis with either *Escherichia coli* viva OM-89 (UroVaxom^®^), bacterial lysate vaccine (StroVac^®^), nasturtium and horseradish root powder (Angocin^®^), D-Mannose or bladder irrigation with saline once daily. Occurring complications under named prophylaxis will be treated according to the current standard of care. 

Primary Outcome Measure: Incidence of symptomatic breakthrough infections.

Secondary Outcomes: Severity of infectious breakouts with antibiotic use, development of antibiotic-resistant (AMR) flora, number of antibiotics used, quality of life, and exploration of health economic assessment variables. 

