### 6.3. Evaluation at 3, 6, 9 and 12 Months (Table 1)

Number of UTI (reported by patient; if externally diagnosed and treated by, e.g., primary caregiver records will be obtained and added to study documentation);Hospital admission due to UTI or severe systemic infection (SOFA Score, SIRS criteria, Antibiotic administration, duration of hospital stays, urine culture);Antibiotic treatment/ treatment with a reserve antibiotic;Urine culture, including susceptibility profile;Rectal swab (optional);Perineal swab (optional);ACSS score;Adverse events during intake;HRQoL measures (subgroup of 30 patients);End at 12 months: patient impression (Likert Scale).

**Table 1 mps-06-00052-t001:** Summary of data collection points.

	Day 0	Month 3	6	9	12
*ACSS*	*X*	*X*	*X*	*X*	*X*
*Recruit*	*X*				
*Rectal swab*	*X ^*		*X ^*		*X ^*
*Perineal swab*	*X ^*		*X ^*		*X ^*
*CRF*	*X*	*X*	*X*	*X*	*X*
*Urine culture*	*X*		*X ^*		*X*

^ optional; ACSS = Acute Cystitis Symptom Score; CRF = Case Report Form.

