## 7. Statistical Considerations

Power analysis was performed to determine an adequate sample size. We considered that these patients suffer 9.4 UTIs per year with an SD of 5.414. Furthermore, we assumed that a reduction of 3 UTIs per year is clinically significant. In order to achieve an effect size of 0.1, 785 participants are necessary (power = 0.87; alpha = 0.05). Furthermore, to achieve an effect size of 0.2, 197 participants are necessary, or for an effect size of 0.3, 88 participants are required, respectively. Data measured on a continuous scale will be expressed as mean, standard deviation, range, and median. Counts and percentages of patients in the categories will be used to convey categorical data. When necessary, T- or Mann-Whitney tests will be performed to determine statistical differences in continuous variables, and Chi-square or Fisher’s tests will be used to test for statistical differences in categorical variables.

Patients with a minimum follow-up of 6 months who remained on the same prophylaxis regimen will be eligible for the final statistical analysis. 

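### The plan does not say whether UTIs are compared per unit of time, so if raw counts are tested, unequal leaving between months 6 and 12 would look like a regimen effect

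*Protocol article*

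**What the plan says.** The outcome is described in two ways. Section 1.1 says "The primary outcome is depicted by the number of breakthrough infections". Section 3 says "Primary Outcome Measure: Incidence of symptomatic breakthrough infections", and the Abstract also uses the word incidence. Neither gives a denominator. At months 3, 6, 9 and 12, Section 6.3 records "Number of UTI (reported by patient; if externally diagnosed and treated by, e.g., primary caregiver records will be obtained and added to study documentation".

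Planned follow-up is fixed in the Abstract: "Patients will be followed for 12 months from the onset of the prophylaxis protocol". Section 7 then sets the analysis population: "Patients with a minimum follow-up of 6 months who remained on the same prophylaxis regimen will be eligible for the final statistical analysis". Time at risk in the final analysis can therefore run from 6 to 12 months.

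Section 7 names two families of between-group test. One, for categorical outcomes, is Chi-square or Fisher. On the other it says "When necessary, T- or Mann-Whitney tests will be performed to determine statistical differences in continuous variables". It mentions no person-time, annualised rate, offset or count model. Its sample-size paragraph does work on a yearly scale (9.4 UTIs per year, SD 5.414, a reduction of 3 per year taken as clinically significant), but the analysis text does not carry that scale over. Section 6.4 records the time point of dropout and the duration of the regimen, so time at risk can be calculated.

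**The concern.** A count of recurrent events grows with time observed. A patient analysed after 6 months has had half the opportunity for UTIs of one analysed after 12. If the counts are compared without reference to time, any difference between regimens in how many patients leave after month 6, or how early, is read as a difference in effectiveness. The arm that loses more patients looks better.

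Unequal leaving is plausible here. The clinician chooses the regimen, and the burdens differ: Section 6.2 has a short vaccination course in one arm and daily intake or daily irrigation throughout in others. Section 6.4 foresees stopping for adverse events, problems of administration and switching. Section 2 says the results are meant to identify candidate regimens for a randomised trial, so a spurious ranking would carry forward.

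**Working it through.** **Inputs from the protocol article.** UTI rate 9.4 per year and SD 5.414 (Section 7); follow-up of 12 months (Abstract); at least 6 months needed for analysis (Section 7).

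**Assumptions.** 785/5 = 157 patients per arm, since no allocation ratio is given. Leaving times spread evenly over months 6 to 12. Leaving unrelated to a patient's own UTI rate. The proportions leaving, since the protocol states no dropout rate. The same true UTI rate in both arms.

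**Step 1: events lost per leaver.** Mean follow-up of a leaver is (0.5 + 1)/2 = 0.75 year. Expected UTIs lost are 9.4 × (1 − 0.75) = 2.35.

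**Step 2: spurious difference between arms.** This is 2.35 × (difference in proportion leaving):
- 10-point gap: 2.35 × 0.10 = 0.24
- 20-point gap: 2.35 × 0.20 = 0.47
- 40-point gap: 2.35 × 0.40 = 0.94

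**Step 3: approximate false-positive rate of a two-sided 5% t-test.** The standard error of a difference in means is 5.414 × √(2/157) = 0.611. With r = spurious difference / 0.611, the rejection probability is about 1 − Φ(1.96 − r) + Φ(−1.96 − r):
- r = 0.235/0.611 = 0.385 gives 6.7%
- r = 0.47/0.611 = 0.769 gives 12.0%
- r = 0.94/0.611 = 1.538 gives 33.7%

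**Step 4: simulation.** Counts were drawn from a gamma-Poisson (negative binomial) distribution with mean 9.4 and SD 5.414 per year, so shape = 9.4²/(5.414² − 9.4) = 88.36/19.91 = 4.44. Each scenario had 4,000 runs with no true difference between arms. The last two columns use time at risk; the rate-ratio test is events over person-time with robust variance.

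| Leaving, arm A vs arm B | Mean difference in raw counts | t, raw | Mann-Whitney, raw | t, annualised | Rate-ratio test |
|---|---|---|---|---|---|
| 20% vs 20% | 0.0 | 5% | 5% | 5% | 5% |
| 10% vs 20% | −0.2 | 7% | 7% | 5% | 5% |
| 10% vs 30% | −0.5 | 12–13% | 13% | 5% | 6% |
| 0% vs 40% | −0.9 | 35–36% | 37–39% | 5% | 5% |

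Ranges cover repeat runs. The simulation agrees with the hand calculation in Step 3. Mann-Whitney on annualised rates also stayed near 5% in every row.

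**Step 5: a harsher pattern.** If all leavers go exactly at 6 months, each loses 9.4 × 0.5 = 4.7 expected UTIs, and a 10-point gap costs 0.47. With 2,000 runs, 10% versus 30% leaving then gives a difference of 0.95 and false positives of 34% (t) and 41% (Mann-Whitney). The rate-ratio test stays at about 5%.

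**The case against.** The strongest objection is that the article does not commit to testing raw counts. The tests are to be used when necessary, for continuous variables, and are not tied to the primary outcome by name. The word incidence and the yearly scale of the sample-size paragraph both leave room for an annualised rate per patient, and on that scale the named tests hold their 5% level, as the table shows. This stands, and it is why the point is conditional. It does not dispose of the point: nothing in the text states annualisation, Section 1.1 says number, and no other between-group method is named.

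A second objection is that an article may leave the count model to an analysis plan. That is fair for the choice of model. But the article itself sets the 6-month minimum and names the tests, and together these leave the scale of the primary outcome open.

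A third is that the larger figures need an extreme contrast between arms. This also stands. A 10-point gap raises the false-positive rate only to about 7%, and equal leaving does no harm.

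Three stronger readings are tempting and should not be drawn:
- *That the plan fixes a biased test of the primary outcome.* It does so on one reading only.
- *That the artefact can exceed the 3-UTI difference of interest, because a 6-month patient has 4.7 fewer expected UTIs than a completer.* This sets a gap between single patients against a difference between group means. Producing 3 UTIs between arms would take an excess of 3/4.7 = 64 percentage points of patients leaving exactly at 6 months. With leaving spread evenly over months 6 to 12, even 100% versus 0% gives only 2.35.
- *That standard errors would be understated because the planned variance (5.414² = 29.3) is well above the mean (9.4).* That would apply to a plain Poisson analysis, which the plan does not propose. The t and Mann-Whitney tests use the observed spread. Overdispersion matters only for choosing the replacement model.

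**Conclusion.** The concern holds in conditional form. The article combines analysed follow-up of 6 to 12 months, a primary outcome without a stated time unit, and tests that use no time at risk. If raw counts are compared, a regimen with more leavers after month 6 is favoured with no true difference. The spurious difference ranges from about 0.2 UTI (7% false positives) at 10% versus 20% leaving to 0.9 UTI (35%) at 0% versus 40%. It disappears when leaving is equal or when time at risk is used.

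These sizes rest on 157 per arm, evenly spread leaving times, and leaving that is unrelated to UTI rate. The proportions leaving illustrate a range and are not predictions. The direction needs only that follow-up length differs by regimen. If leavers have higher UTI rates, the observed gap may shrink, but their truncated counts still understate what 12 months would have shown.

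The point concerns only patients who leave between months 6 and 12. Those who leave before 6 months or switch regimen are not eligible for the final analysis. That is a separate selection problem, and accounting for time at risk does not solve it.

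**What to change.** Define the primary outcome once, in the same words throughout, as UTI episodes per person-year on the regimen, counted from its start. Compare regimens with a negative-binomial model (or another rate model with robust variance) with log follow-up time as offset and regimen as a five-level factor, and report rate ratios with 95% confidence intervals. Keep the t and Mann-Whitney tests for describing continuous baseline variables.

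At minimum, state that the named tests will be applied to annualised per-patient rates. This also keeps the error near 5% when leaving is unrelated to UTI rate. It gives a 6-month patient the same weight as a 12-month one, so some efficiency is lost, but that is not a bias.

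Report the distribution of follow-up time and the proportion leaving between months 6 and 12 by regimen, so that readers can judge how far it differs.

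The cost is a change of wording in Sections 1.1, 3 and 7 and the Abstract. The timing data are already collected under Section 6.4, so no new data or patients are needed.

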### 4.2. Exclusion Criteria

Patients practising ISC with augmented bladder or continent pouches;Inability to consent;Intention-to-treat analysis for dropouts;Failure to provide consent;MDR pathogens in previous episodes of UTIs;Antibiotic prophylaxis in the months before study enrolment.

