### 6.2. Non-Antibiotic Prophylaxis Regimen

UroVaxom (OM-89) will be administered as a standard regimen: once daily for three months with a three-month pause following and three ten-day cycles at 7, 8 and 9 months.,StroVac (bacterial lysate vaccine) standard regimen: three vaccines in 6–12 weeks with two weeks between each vaccination *.Angocin twice daily for the duration of the study.D-mannose (oral dose 2 g) once daily for the duration of the studyBladder irrigation with saline (0.9%; 250 mL) once per day for the duration of the study.

* In case of restricted drug availability due to country-specific authorisation of vaccines, additional treatment arms with similar mechanisms of action will be opened and analysed as a subgroup. If necessary, amendments to the protocol will be issued, and additional ethics approval will be requested.

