### 6.4. Documentation of Stop Criteria/Study Dropout

Reason for dropout;Time Point of dropout;UTI;Sepsis;Adverse events;Problems of administration of the drug;Duration of non-antibiotic regimen;Switch to another prophylaxis regimen/which one.

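### Restricting the final analysis to patients who stay on one regimen for at least 6 months ties inclusion to the outcome, can understate infection rates, and can bias the regimen comparison

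*Protocol article*

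**What the plan says.** Section 7 (Statistical Considerations) states: "Patients with a minimum follow-up of 6 months who remained on the same prophylaxis regimen will be eligible for the final statistical analysis". No other analysis population is defined in the article. It does not say whether remaining on the regimen means for 6 months or for all 12.

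The other relevant statements are:

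- Section 3 (Design): "Primary Outcome Measure: Incidence of symptomatic breakthrough infections". The Abstract also names adverse events as a secondary outcome.
- Abstract: "Patients will be followed for 12 months from the onset of the prophylaxis protocol". The clinician chooses the regimen. Section 6.5 says assessors are not blinded.
- Section 6.4 (Documentation of Stop Criteria/Study Dropout) records "Reason for dropout;Time Point of dropout;UTI;Sepsis;Adverse events;Problems of administration of the drug", and also "Switch to another prophylaxis regimen/which one".
- Section 6.2 gives regimens of very different length. The StroVac course is three vaccinations within 6–12 weeks. UroVaxom is intermittent. Three regimens are daily throughout, for example "Angocin twice daily for the duration of the study"; the other two are D-mannose and saline irrigation.
- Section 4.2 (Exclusion Criteria) contains the item "Intention-to-treat analysis for dropouts".

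**The concern.** Membership of the analysis set is decided by events after baseline, and some of those events are close to the outcome. If repeated breakthrough infections prompt a patient or an unblinded clinician to stop or switch before the patient qualifies, that patient's infections leave the primary result. Early stopping for intolerance removes adverse events in the same way.

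Two results are at stake. One is the breakthrough incidence in each arm, which is the stated primary outcome. The other is the comparison between regimens. Section 2 says the long-term goal is to pick safe and effective candidates for a randomised trial. A regimen that loses more of its poor responders than another would look better than it is.

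**Working it through.** **Plan's own figure.** The article states no exit rate, retention rate or bias allowance, so there is nothing to reproduce on this point. The sample size of 785 does not enter the argument.

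**Inputs from Section 7.** Mean 9.4 UTIs per year, SD 5.414, and a clinically relevant reduction of 3 per year.

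**Assumptions, not in the article.**
- Equal arms of 785/5 = 157.
- The 9.4 background rate also holds on prophylaxis.
- Counts are gamma-Poisson.
- A patient with 6 or more UTIs in the first 6 months (expected count 4.7) leaves the set with probability q. Nobody else leaves, and those retained are counted over 12 months.

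**Step 1, count model.** Shape = 9.4² / (5.414² − 9.4) = 88.36 / 19.91 = 4.44.

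**Step 2, who is at risk of exit.** Under this model 33.9% of patients have 6 or more UTIs in the first half-year. Their mean annual count is 14.69, and that of the rest is 6.68. Check: 0.339 × 14.69 + 0.661 × 6.68 = 9.4.

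**Step 3, retained mean.**

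Mean(q) = [0.661 × 6.68 + 0.339 × (1 − q) × 14.69] / (1 − 0.339q)

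- q = 0: 9.4
- q = 0.25: (4.415 + 3.735) / 0.915 = 8.9, with 8.5% excluded
- q = 0.5: (4.415 + 2.490) / 0.8305 = 8.3, with 17% excluded
- q = 0.8: (4.415 + 0.996) / 0.729 = 7.4, with 27% excluded

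**Step 4, two arms with equal true rates.** Rejection is for a two-sided t-test at 0.05, by simulation.

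| Exit in arm A / arm B | False difference per year | Rejection |
|---|---|---|
| 50% / 50% | 0 (both arms about 8.3) | about 5% |
| 50% / 40% | about 0.25 | about 7% |
| 50% / 25% | about 0.6 | about 16–17% |
| 30% / 0% | about 0.6 | about 16% |
| 50% / 0% | about 1.1 | about 42% |
| 80% / 0% | about 2.0 | about 91% |

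**Step 5, true rates that differ.** Here the true rates are 6.4 and 9.4, a difference of 3.0. Patients leave with probability 0.3–0.8 after 3 or more, or 4 or more, UTIs in either of the first two quarters. The difference seen among those retained is:

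- same rule in both arms: 1.9 to 2.8
- exit only in the worse arm: 0.5 to 2.4
- exit only in the better arm: 3.3 to 4.4

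So even an identical exit rule in both arms shrinks a real difference, because the worse arm loses more of its high counts.

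**Step 6, power.** With 50% retained (78 per arm), power to detect 3 UTIs per year at SD 5.414 is still about 0.93 for one pairwise test at two-sided 0.05. The main harm is bias, not lost numbers.

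**Step 7, Sections 4.2 and 7 side by side.** The Section 4.2 item cannot work as an exclusion criterion. Read as an analysis statement, it points to keeping dropouts, whereas Section 7 removes those who left before 6 months or changed regimen. The article does not say which governs.

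**The case against.** **Failures are not removed as such.** A reader might infer that every patient whose prophylaxis fails is excluded. The article does not say so. A patient with many UTIs who stays on the regimen is kept. Section 6.4 is a documentation list that mixes reasons with items such as timing and duration, and it sets no rule that a UTI ends participation. Its heading makes outcome-related exit plausible but does not establish it. This objection stands, and the point is limited to failures that lead to stopping, switching or dropout.

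**Comparative bias is not demonstrated.** A reader might also take the 42% as the false-positive rate to expect. It belongs to a one-sided case with heavy exit in one arm and none in the other. With equal exit and equal true rates the rejection rate stays near 5%. This stands for the comparison. It does not protect the incidence in each arm, which still falls from 9.4 to about 8.3.

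**The arm-specific argument has limits.** It is tempting to say that a StroVac patient can hardly leave the regimen. The article does not say that, and a patient who moves to another regimen after the vaccinations may not count as having remained on the same one. Different regimen lengths make unequal exit plausible, no more.

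**An on-regimen analysis is a legitimate question in a non-randomised, candidate-finding cohort.** True, but here it is the only analysis set stated. Confounding by the clinician's choice is unavoidable in this design; this selection is avoidable.

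**Section 4.2 may already intend to keep dropouts.** The item is a misplaced fragment tied to no analysis, too vague to override the explicit sentence in Section 7.

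**Conclusion.** The concern holds in a limited form. The Section 7 rule conditions the final analysis on persistence after baseline, and the recorded stop and dropout items include the primary outcome and adverse events. If such events drive exit, infection and adverse event rates are understated in each arm. The comparison is distorted if exit differs by arm or true rates differ.

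Size and direction cannot be read from the article. Under the stated assumptions the false difference runs from 0 (equal exit) through about 0.6 (50% against 25%) to about 1.1 (50% against none), against a relevant difference of 3 UTIs per year. These figures rest on assumed exit rates, equal arms and the background rate of 9.4. They show what the rule can do and do not predict what this study will find. Sections 4.2 and 7 must also be reconciled, since a choice between them made after the data are seen could change the result.

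**What to change.** - In Section 7, make the primary analysis set all enrolled patients who started a regimen, analysed by the regimen started. Count UTIs over all observed person-time from day 0, which also handles unequal follow-up.
- Keep the present set as an on-regimen sensitivity analysis, and state whether staying on the regimen means 6 or 12 months.
- Remove the intention-to-treat item from Section 4.2 and put a clear statement in Section 7.
- Continue the planned 3-monthly data collection after a stop or switch where possible; otherwise censor at last contact.
- Report exit by arm with its recorded reasons.

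**Cost.** Mostly wording, since the 3-monthly evaluations and the stop and switch records are already planned. Following patients after a switch is a small procedural addition, because the article lists switching under dropout and does not say that switchers stay under observation. The estimate becomes the effect of starting a regimen, which switching may dilute; the on-regimen analysis can be shown beside it.

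### Section 7 limits the final analysis to patients who persist on their regimen, so UTI-driven stopping or switching can bias the comparison, and the intention-to-treat phrase in Section 4.2 is not reconciled with it

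*Protocol article*

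**What the plan says.** Section 7 (Statistical Considerations) fixes the analysis set: "Patients with a minimum follow-up of 6 months who remained on the same prophylaxis regimen will be eligible for the final statistical analysis".

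Section 1.1 gives the purpose: "The main aim of our study is to identify the comparative clinical effectiveness of non-antibiotic prophylaxis regimens". Section 3 gives the outcome: "Primary Outcome Measure: Incidence of symptomatic breakthrough infections".

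Section 6.4, on documenting stop criteria and dropout, asks for the reason and time point and then lists "UTI;Sepsis;Adverse events;Problems of administration of the drug;Duration of non-antibiotic regimen;Switch to another prophylaxis regimen/which one".

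Section 4.2 contains, among the exclusion criteria, the phrase "Intention-to-treat analysis for dropouts".

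On follow-up, the Abstract says "Patients will be followed for 12 months from the onset of the prophylaxis protocol". Section 6.3 plans UTI counts at 3, 6, 9 and 12 months and adds, for events handled elsewhere, "if externally diagnosed and treated by, e.g., primary caregiver records will be obtained and added to study documentation".

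**The concern.** The rule in Section 7 selects patients on post-baseline persistence. In a prophylaxis study, an obvious reason to abandon a regimen is that it is not preventing infections, and infections are the primary outcome. Patients with many early UTIs may therefore be under-represented among those analysed, which makes every regimen look better than it is.

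For a comparison of regimens, the more serious problem is unequal UTI-driven stopping. If patients or clinicians give up sooner after breakthrough infections on one regimen than on another, the first regimen loses more of its high-count patients and looks better for that reason alone. Section 2 says that the results are meant to identify candidates for a later randomised trial, so a distorted ranking would have consequences.

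The phrase in Section 4.2 points to keeping dropouts in an analysis, but it is not a criterion for excluding anyone. Nothing in the document says how it relates to Section 7 or which set carries the main comparison.

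**Working it through.** **Inputs from the document (Section 7):** 9.4 UTIs per year, SD 5.414, a relevant reduction of 3 UTIs per year, 785 patients. The document gives no stopping or switching rate, so there is no planned figure to reproduce here.

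**Assumptions (mine):** UTI counts are gamma-Poisson (negative binomial). A patient whose first-quarter count X reaches a trigger T stops or switches at month 3 with probability p, and so is outside the Section 7 set. T and p are varied.

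**Step 1, dispersion.** k = 9.4² / (5.414² − 9.4) = 88.36 / 19.91 = 4.44.

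**Step 2, who meets the trigger.** X has mean 9.4/4 = 2.35. The expected 12-month total given X = x is x + 0.75 × (k + x) / (k/9.4 + 0.25).

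- T = 3: 39.6% of patients meet it; their 12-month mean would be 13.25.
- T = 5: 12.8%; mean 16.87.
- T = 6: 6.7%; mean 18.77.

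**Step 3, mean in the retained set.** With P the share meeting the trigger and M their mean: retained mean = (9.4 − p × P × M) / (1 − p × P). For T = 3, p = 0.5: (9.4 − 0.198 × 13.25) / 0.802 = 8.45.

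**Step 4, false difference** between two regimens that both truly run at 9.4, one with no stopping and one with stopping probability p:

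| Trigger | Retained mean, p = 25% | Retained mean, p = 50% | False difference |
|---|---|---|---|
| 3 or more | 8.98 | 8.45 | 0.42 to 0.95 |
| 5 or more | 9.15 | 8.89 | 0.25 to 0.51 |
| 6 or more | 9.24 | 9.08 | 0.16 to 0.32 |

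The sign always favours the regimen with more UTI-driven stopping. With T = 3, about 707 or 630 of 785 would remain if all regimens stopped at that rate. Without overdispersion (Poisson), the T = 3 false differences fall to 0.17 and 0.39.

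**Step 5, equal stopping in both regimens, true difference 3 (9.4 vs 6.4), T = 3, p = 25% / 50%.**

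- Same k: 8.98 − 6.16 = 2.82 / 8.45 − 5.89 = 2.56.
- Same SD (k = 1.79 at rate 6.4): 2.96 / 2.87.
- Poisson: 2.94 / 2.84.

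The true difference of 3 therefore stays at about 2.6-3.0.

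**Step 6, stopping unrelated to UTI count.** If a share c leaves at random, the retained mean is (9.4 − 9.4c) / (1 − c) = 9.4. No bias of this kind arises.

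**Cross-check with another mechanism.** A simulation in which each UTI carries a fixed chance of stopping (2% on one regimen, 10% on the other, equal true rates of 9.4) gives a false difference of about 1.0 UTI per year if persistence is required to month 6. It gives about 1.8 if persistence is required for all 12 months. Section 7 does not say which applies. These rates are also assumed.

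**The case against.** **Section 6.4 is a recording list.** A reader might infer that a UTI is a criterion that ends follow-up. The text does not say so: it asks sites to document items, and regimen duration and switching are listed separately. Section 3 says that complications are treated by standard of care, and the Abstract and Section 6.3 point to counting over 12 months. This stands. What remains is that stopping and switching are foreseen, UTI is listed in that context, and Section 7 removes those who stop early or switch.

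**The two analysis statements might coexist.** A reader might infer a flat contradiction. The Section 4.2 phrase is too short to carry that: it could mean a separate analysis covering dropouts. The safe statement is that it is misplaced and not reconciled with Section 7. The existence of an unseen analysis plan does not dispose of the point, because the protocol article itself fixes the restrictive set.

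**Burden is not the mechanism.** Section 6.2 has three regimens taken or applied throughout the study, while StroVac is given as "three vaccines in 6–12 weeks with two weeks between each vaccination". A reader might infer that the more burdensome regimens will be left more often and so look better. Step 6 shows that this follows only if leaving is related to UTI count. The dosing schedules alone do not establish the bias.

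**The size depends on the trigger.** Three UTIs in a quarter is close to the average of 2.35, and about 40% of patients reach it. A stricter trigger roughly halves the effect or more. This also stands, so both ranges are shown.

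**An on-regimen set is a recognised choice** when looking for candidates for a later trial, and an all-enrolled analysis is diluted by switching. That supports keeping the same-regimen set as a secondary analysis. It does not support making it the only stated set for a comparison of effectiveness.

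**Conclusion.** The point holds as a should-fix matter, with medium confidence. Section 7 states a rule under which the primary outcome can decide who is analysed. The direction is clear if stopping or switching is driven by UTIs: rates are understated, and unequal UTI-driven stopping favours the regimen with more of it.

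The size cannot be derived from the document. Under the trigger model with 25-50% stopping on one regimen and none on the other, the false difference is about 0.4-1.0 UTIs per year (trigger 3) or 0.2-0.5 (trigger 5 or 6), against a stated relevant reduction of 3. With equal stopping at those rates the comparison is nearly intact. It would be wrong to conclude that the comparison is invalid whatever happens, or that a particular regimen will be favoured. Confounding by the clinician's choice of regimen remains under either analysis set; this is an additional and avoidable bias.

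**What to change.** In Section 7:

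1. Make the main comparison all enrolled patients by starting regimen, using UTIs over time at risk up to 12 months.
2. State that the planned 3, 6, 9 and 12-month UTI counts continue after a stop or switch unless consent is withdrawn. Whether to stop or switch remains a clinical decision.
3. Keep the 6-month same-regimen set as a secondary analysis.
4. Move the intention-to-treat statement here from Section 4.2.

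**Cost.** Mostly wording, since the contacts and the retrieval of outside records are already planned. Sites must stay in touch with patients who have stopped.

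There is also some dilution. If every stopper on the worse regimen moved to the better one (true difference 3, trigger 3), post-stop UTIs per enrolled patient would be 0.892 or 1.784 at 25% or 50% stopping. Multiplied by 1 − 6.4/9.4 = 0.319, this removes 0.28 or 0.57, so a true 3 would read about 2.7 or 2.4. The secondary same-regimen analysis is there to be read alongside that result.
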